### Limitations

Due to the significant variability in TSH levels, we cannot guarantee whether the diagnosis of patients has been affected by the fluctuations in TSH. We can only strive to have patients undergo two repeated measurements whenever possible, and make an effort to select the same time point for testing. Considering the significance of T_4_, we plan to establish a diagnostic indicator that combines both T4 and TSH.

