## Introduction

Subclinical hypothyroidism (SCH) is characterized by elevated serum thyroid-stimulating hormone (TSH) and normal thyroid hormone levels (1). As TSH is considered a good indicator of thyroid function, the diagnosis of SCH is primarily based on TSH levels. However, this can lead to overdiagnosis and overtreatment in elderly patients with SCH, as their TSH levels may naturally increase with age without indicating an underlying thyroid dysfunction (2).

Many studies have found that the incidence rate of SCH increases significantly with age (3, 4), which suggests that we need to consider the impact of aging on the hypothalamic-pituitary-thyroid (HPT) axis. For example, aging may weaken the circadian rhythm of TSH and reduce its responsiveness (5). According to the cross-sectional National Health and Nutrition Examination Survey (NHANES) III, the average TSH of adults aged 80 is 69% higher than that of adults aged 20 (6, 7). Data from Scottish, and Australia also confirm that TSH level increases with age (8–10). Our previous epidemiological survey in ten cities indicated that the prevalence of SCH in people over 65 years old was 19.87% according to the current TSH reference interval, but when the age-specific TSH reference range was used, the prevalence decreased to 3.3% (3). Although the mechanism is unclear, the increase in TSH in the elderly may be a normal phenomenon associated with aging. When the current diagnostic criteria are used, many elderly patients with no clinical significance will be diagnosed.

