Prospective research on the natural outcome of the elderly indicated the above problem. In 2004, a study from Spain followed up 107 elderly patients with SCH over 55 years of age for 6 years (11), and the proportion of patients’ disease progression, maintenance, and recovery were 26.8%, 35.8%, and 37.4% respectively, that is, only a few patients had significant progress. In 2012, an American study conducted a 4-year follow-up of 459 elderly patients with SCH over 65 years old and found that 56% of the patients were in the state of SCH maintenance in the second and fourth years of follow-up (12). In addition, the remission rate of TPOAb-negative patients is significantly higher than that of TPOAb-positive patients. In 2017, a Chinese study conducted a 3-year follow-up of 505 patients with SCH over the age of 40 and found that only 3.4% had progressed, while 43.8% were in maintenance, and 49.7% returned to normal (13). It was also believed that TPOAb, TSH levels, creatinine, and total cholesterol levels were related to different outcomes of SCH. That is, many elderly patients with SCH may have stable or even recovery of their condition without any intervention, while only a few of them have progressed and need treatment, which suggests that using the current unified TSH reference interval of the entire population to diagnose SCH in the elderly may lead to overdiagnosis and overtreatment. To avoid this, it is recommended to establish age-specific TSH reference ranges for the elderly to better identify those who may require treatment. This approach can help prevent unnecessary interventions in patients with SCH and reduce potential adverse effects of overtreatment.

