### Inclusion criteria and exclusion criteria

Inclusion criteria:

Elderly patients with SCH will be included according to the elderly and the general population-specific reference ranges, respectively.

(1) Inpatients and/or outpatients aged≥60 years.(2) The levels of free triiodothyronine(FT_3_) and FT_4_ are within the normal range.(3) TSH is greater than the upper limit of the normal reference range (old standard) and less than the upper limit of the normal reference range (new standard).

Exclusion criteria:

(1) Does not meet the inclusion criteria, does not sign the consent form, or participates involuntarily.(2) Exit halfway due to various reasons.(3) Unable to cooperate with the project team to complete all inspection contents.(4) Other factors leading to TSH increase. 1) increased TSH caused by measurement errors; 2) convalescence stage of the euthyroid sick syndrome; 3) central hypothyroidism; 4) renal insufficiency; 5) lack of glucocorticoids; 6) the recovery stage of thyroid function in subacute thyroiditis; 7) having taken amiodarone or lithium; 8) other interfering factors.

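### Entry on one TSH value just above the general limit is allowed, so the recovery and TSH-change results will include regression to the mean, chiefly in patients between the old and new limits

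*Protocol article*

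**What the plan says.** The third inclusion criterion defines entry by a TSH band: "TSH is greater than the upper limit of the normal reference range (old standard) and less than the upper limit of the normal reference range", the second limit being the new standard. It requires no repeat value and no interval between tests. Recruitment covers "Inpatients and/or outpatients aged≥60 years". One exclusion removes "increased TSH caused by measurement errors", and others remove named causes of a raised TSH.

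Under Limitations the protocol says "we cannot guarantee whether the diagnosis of patients has been affected by the fluctuations in TSH", and then "We can only strive to have patients undergo two repeated measurements whenever possible", with an effort to test at the same time point. A second value is therefore sought but not required.

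The Introduction sums up earlier cohorts by saying that "many elderly patients with SCH may have stable or even recovery of their condition without any intervention", and reads this as a sign that the unified range may over-diagnose. Data analysis then plans to analyse natural outcomes under the different reference intervals. The Discussion presents the study of natural outcomes as the means of confirming that an age-specific interval is needed. Variables measured repeatedly are to be compared by paired t-test.

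**The concern.** A patient chosen because one reading exceeded a limit will on average read lower next time, because part of the first excess was ordinary within-person variation. If the patient's usual TSH is close to the limit, the next value often falls below it and looks like spontaneous recovery. Such a patient shows what unconfirmed testing does. The case says nothing about whether the limit is wrong for the patient's age.

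The direction matters because the effect is uneven. Patients between the old and new limits start close to the old limit and cross back easily; patients above the new limit start far from it. Chance alone would therefore produce more recovery in the group that the age-specific range would reclassify as normal. The stated paired t-test would also register the drop from a selected first value as change.

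**Working it through.** The protocol gives no figure for regression to the mean and no within-person variance, so there is nothing to reproduce. The calculation below only illustrates the size.

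**Inputs from the document (Introduction)**
- Share above the old limit, age over 65: "the prevalence of SCH in people over 65 years old was 19.87% according to the current TSH reference interval".
- Share above the age-specific limit: "when the age-specific TSH reference range was used, the prevalence decreased to 3.3" per cent.
- The band between them holds 19.87 − 3.3 = 16.57% of that population, or 16.57/19.87 = 83% of those labelled under the old range.

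**Assumptions not in the document**
- Standardised log TSH is normal, and each reading is a stable set-point T plus independent noise E, with Var(T) = r and Var(E) = 1 − r. There is no true change.
- The test-retest correlation r is unknown. The main illustration uses 0.8–0.9; the table shows 0.5–0.95.

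**Cut-offs.** Old limit z = Φ⁻¹(1 − 0.1987) = 0.846. New limit z = Φ⁻¹(1 − 0.033) = 1.838.

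**Formula.** For set-point t, let B(t) be the chance that a reading lies in the band, U(t) the chance that it exceeds the old limit, and L(t) = 1 − U(t). Averaging over T:
- (a) single-value entry, next reading below the old limit: E[B·L]/E[B];
- (b) first reading above the new limit: as (a), with the chance of exceeding the new limit in place of B;
- (c) second baseline value also raised: E[B·U·L]/E[B·U];
- (d) as (c), with recovery required at both of two given visits: E[B·U·L²]/E[B·U].

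| r | (a) band, one value | (b) above new limit | (c) band, second value raised | (d) as (c), two visits |
|---|---|---|---|---|
| 0.5 | 60% | 38% | 47% | 27% |
| 0.7 | 49% | 17% | 34% | 17% |
| 0.8 | 41% | 7.5% | 27% | 12.4% |
| 0.85 | 36% | 4% | 23% | 10% |
| 0.9 | 30% | 1% | 18% | 7.5% |
| 0.95 | 21% | <0.1% | 12% | 5% |

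**Column (d) is for one given pair of visits.** If any consecutive pair among four visits counted, L² becomes 3L² − 2L³ and the result is 23% (r = 0.8) or 14% (r = 0.9). The like-for-like comparison is any single low reading among four visits after single-value entry, which uses 1 − (1 − L)⁴ and gives 71% or 55%. The pair of visits therefore has to be named.

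**TSH change.** The mean of a single qualifying value in the band is (φ(0.846) − φ(1.838))/0.1657 = (0.2789 − 0.0736)/0.1657 = 1.24 SD. The expected next value is r × 1.24, which is 0.99 at r = 0.8 and 1.12 at r = 0.9, with no true change. Using a second value that also had to be raised does not cure this: its mean is 1.41, and the next value averages 1.21 at r = 0.8 (1.36 and 1.26 at r = 0.9).

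**The case against.** **Recovery is not a named endpoint event.** The abstract names an FT4 decrease for patients over 80, and TSH ≥10 or an FT4 decline for those aged 60–80. This stands. A reader might infer that the study will falsely confirm over-diagnosis. The documents do not support that: the bias acts on the natural-outcome and TSH-change results, and those are only part of the evidence. Entrants whose usual TSH is normal may also dilute progression rates, but that is less direct.

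**Transient rises are already excluded.** Measurement error, convalescence from euthyroid sick syndrome, recovery from subacute thyroiditis and interfering drugs are all listed, and testing at the same time point is intended. This weakens any argument resting on inpatients in particular. It does not cover ordinary within-person variation in an otherwise eligible patient.

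**The size is assumed.** This stands. The prevalences come from a survey of people over 65, not from hospital patients aged 60 and over, and r is not given. It is tempting to set 30–41% beside the 37.4% and 49.7% recovery in the cited cohorts and call that recovery artefact. Those cohorts were over 55 and over 40, were followed for 6 and 3 years, and are described as SCH generally rather than as the band between the limits. The comparison cannot show how much of their recovery was chance. The contrast with patients above the new limit also presumes that such patients are followed. The third criterion describes only the band, while the follow-up section describes patients screened under both ranges.

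**The limitation is disclosed, and an analysis plan may deal with it.** Disclosure does not remove the bias, and the Limitations text does not link fluctuation to recovery. An analysis plan could set the rules proposed here, but it cannot supply a second baseline value that was never taken.

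**Conclusion.** The point holds for the recovery and TSH-change results. The text permits single-value entry in the range where regression to the mean matters most, and under the model the artefact is larger in the group expected to be over-diagnosed. In the no-change model with r of 0.8–0.9, 30–41% of band patients appear to recover at the next test, against about 1–8% of patients above the new limit. Over wider assumptions the band figure runs from 21% (r = 0.95) to 60% (r = 0.5). Some regression is present for any r below 1; its size rests on the assumed correlation, the log-normal model and the borrowed prevalences. These results would tend to favour the over-diagnosis conclusion.

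A reader might also infer that single high readings inflate the TSH ≥10 endpoint and that it should be confirmed at a second visit. Nothing in the documents sizes such an effect. Under Study follow-up assessments, treatment can start at the first such value in patients aged 60–70, and with symptoms in those aged 71–80. The next six-monthly value could then be on treatment, and a two-visit rule would miss real events.

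**What to change.** 1. For analysis, count recovery only when TSH is below the general limit at two consecutive scheduled six-monthly visits while untreated. Name the pair of visits used for the main estimate.
2. Base the main recovery estimate on patients with two raised baseline values. Record for each patient whether entry rested on one value or two, and show single-value entrants separately.
3. For TSH change, do not use the qualifying value as baseline. Use a later value that played no part in selection, or correct for regression with the within-person variance estimated from the repeats.
4. Leave the TSH ≥10 endpoint as defined, and report it by single versus confirmed baseline.

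Steps 1 and 2 together bring the artefact for a given pair of visits to about 7–12% at r of 0.8–0.9.

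**Cost.** The six-monthly visits are already planned and the second baseline sample is already sought, so these steps add no scheduled visit. Recovery is ascertained one visit later, and the main recovery estimate rests on fewer patients. If all 438 were band entrants and all were retested, the model would confirm 59–70% of them: 438 × 0.588 = 258 to 438 × 0.701 = 307. Making confirmation an entry rule would also work but is dearer: 438/0.701 = 625 to 438/0.588 = 745 candidates for the same enrolment, within a recruitment window of about one year. It is not needed for the steps above.

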## Discussion

The specific TSH reference interval of elderly patients with SCH and its management deserve attention (34). In recent years, experts have recognized that the management of elderly patients with SCH needs to follow the principle of individualization (35), and much current research indicated that L-T_4_ has not shown any improvement in the treatment of cardiovascular disease mortality, cognitive function, depression, fatigue, hypothyroidism and other symptoms of elderly patients (36–40), which make us consider that the reference range of TSH for the elderly needs to be revised. Distinguishing from the reference interval of TSH for the whole population will effectively identify the truly meaningful patients with SCH, avoid over-diagnosis and save social resources.

To confirm its necessity and establish an age-specific TSH reference interval, we conducted this prospective study of the natural outcomes of elderly patients with SCH diagnosed by different reference ranges of TSH. In addition, the economic benefits will also be evaluated. In a word, our study will facilitate the accurate discrimination of high-risk patients in future clinical diagnosis and treatment, and avoid overdiagnosis and overtreatment.

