### Research objectives and main results

The goal of this study is to prospectively follow up on elderly patients with SCH who are diagnosed using age-specific TSH reference intervals and non-age-specific TSH reference intervals, which aims to establish TSH reference intervals for different age groups to improve the diagnosis and management of SCH in the elderly. The main outcomes being assessed include thyroid function, hypothyroidism-related symptoms, cardiovascular events, cognition, depression, and fatigue, as well as economic and social benefits analysis. The above information will help make informed decisions about the best course of treatment for elderly patients with SCH.

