### Study follow-up assessments

When a patient has FT_4_ levels below the lower limit of the normal reference range during follow-up, follow-up is terminated and thyroid hormone replacement therapy will be initiated. For patients aged 60 to 70 years, start treatment when TSH≥10mIU/L. For patients aged 71 to 80 years, treatment begins when TSH≥10 mIU/L and is accompanied by symptoms of hypothyroidism. Normal value reference ranges will be established based on the TSH levels of 120 normal elderly individuals over 60. Elderly SCH patients screened according to the TSH reference interval in the normal population and the elderly population will be followed up every 6 months, including the subclinical hypothyroidism questionnaire, the Montreal Cognitive Assessment-Basic (MoCA-B), Hamilton Depression Scale (HAMD), Hypothyroidism Symptom Questionnaire (SRQ), frail scale(FRAIL), fatigue scale, EQ-5D, thyroid function, blood lipid analysis, carotid color ultrasound, and thyroid ultrasound. The estimated sample size is 438. Patients diagnosed with different TSH reference intervals will be compared for cognitive function, depression scores, hypothyroidism, fatigue severity, carotid atherosclerosis, lipid profile, and cardiocerebrovascular complications. Besides, TSH reference intervals will be applied to calculate medical costs and evaluate the economic benefits of multiple follow-ups of patients with SCH. The research design can be seen in **Figure 1**.

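### Comparing patients by the TSH interval that labels them can show that TSH level matters after age 60, but not that the limit must differ by age

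*Protocol article*

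**What the plan says.** The Protocol article states the goal in two places. Under Research objectives and main results, the study "aims to establish TSH reference intervals for different age groups to improve the diagnosis and management of SCH in the elderly". In the Discussion the reason given is: "To confirm its necessity and establish an age-specific TSH reference interval, we conducted this prospective study".

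The population has no younger members. The first inclusion criterion is "Inpatients and/or outpatients aged≥60 years", and the reference sample is also elderly: "Normal value reference ranges will be established based on the TSH levels of 120 normal elderly individuals over 60" (Study follow-up assessments).

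The outcome comparison is described in the same section: "Patients diagnosed with different TSH reference intervals will be compared for cognitive function, depression scores, hypothyroidism, fatigue severity, carotid atherosclerosis, lipid profile, and cardiocerebrovascular complications". Data analysis repeats that outcomes will be analysed by diagnosing interval and names a Cox model and paired t-tests. No section names a comparison of patients of different ages at the same TSH.

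Two further passages bear on this. Inclusion criterion 3 requires that "TSH is greater than the upper limit of the normal reference range (old standard) and less than the upper limit of the normal reference range" under the new standard. The Methods part of the Abstract defines the endpoint event differently by age: over 80 it is an FT4 decrease alone, while at 60-80 it is a TSH of at least 10 or an FT4 decline.

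**The concern.** The elderly limit lies above the general one, so patients above the elderly limit are a subset of those above the general limit. Once the two groups are made disjoint, what separates them is mainly TSH level. If risk rises with TSH in the same way at every age, the group with higher TSH still does worse and the comparison is still positive.

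A positive result could therefore be reported as confirming that limits must depend on age when the data show only that higher TSH goes with worse outcomes after 60. The stated conclusion would not follow from the comparison meant to support it.

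**Working it through.** **1. What the groups are.** The Introduction gives a prevalence in people over 65 of 19.87% under the current interval and 3.3% under the age-specific range. The share of labelled patients above the higher limit is 3.3 / 19.87 = 16.6%. Of 438 patients, 438 × 0.166 ≈ 73 would lie above it and 365 between the limits. This assumes that both groups enter and that the survey ratio applies to this cohort. The article gives no inputs for 438, so there is no derivation to reproduce, and the argument does not depend on it.

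**2. What each claim needs.** The article uses the idea of an age-specific limit in two senses.

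| Sense | Where | What outcome data would need | Named in the article? |
|---|---|---|---|
| Different limits for different elderly age groups | Research objectives | Risk at the same TSH compared across ages | No |
| Elderly limit differs from the whole-population limit | Abstract, inclusion criteria, follow-up section, Discussion | Risk at the same TSH in elderly and younger adults | No; no one under 60 is enrolled |

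**3. Can the comparison tell the cases apart?** Assumed inputs: ages uniform 60-90; TSH equal to 4.2 plus an exponential with mean 1.55, capped below 10; groups split at 7; 438 patients; two-sided 5% test; 4,000 cohorts per case. In cases A and B the event risk is 26.8% above the true threshold (the six-year progression figure in the Introduction) and 10% below it (assumed). In case C the log-odds of an event are −2.4 + 0.3 × (TSH − 4.2).

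The share above 7 is exp(−2.8/1.55) = 0.164, or 72 patients.

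| Case | Risk above 7 | Risk below 7 | Significant |
|---|---|---|---|
| A. One threshold of 7 at all ages | 26.7% | 10.0% | 94% |
| B. Threshold 6, 7, 8 by decade of age | 24.1% | 11.0% | 81% |
| C. Risk rises smoothly with TSH, age irrelevant | 24.4% | 11.1% | 82% |

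Case B can be checked by hand. The shares above 6 and 8 are exp(−1.8/1.55) = 0.313 and exp(−3.8/1.55) = 0.086.
- Above 7, the two younger decades have risk 26.8%. The oldest has 10 + (0.086/0.164) × 16.8 ≈ 18.8%. The mean is (26.8 + 26.8 + 18.8)/3 = 24.1%.
- Below 7, the youngest decade has 10 + [(0.313 − 0.164)/0.836] × 16.8 ≈ 13.0% and the others 10%. The mean is 11.0%.

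Cases B and C give practically the same result, although age matters in one and not in the other.

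**4. Same question with hazards.** Follow-up is 2 to 3 years (inclusion December 2022 to December 2023, data to December 2025), so 2.5 years on average. From 26.8% in 6 years, the yearly rate is −ln(0.732)/6 = 0.052, giving 438 × (1 − e^(−0.13)) ≈ 53 events. From 3.4% in 3 years, the same steps give about 12.

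In simulations where hazard depended on TSH only, decade-specific limits were set against one higher limit. Assumptions: general limit 4.5, log-TSH SD 0.6, age slope 0.012 per year, hazard ratio 2-4 per TSH doubling, 400 cohorts per setting.

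| Setting | Decade-specific limits significant | Single limit significant |
|---|---|---|
| 53 events, TSH not capped | 32-95% | 34-95% |
| 53 events, TSH capped below 10 | 12-48% | 13-51% |
| 12 events | 4-42% | 5-44% |

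The two groupings stayed within 3 percentage points in every setting. A TSH-by-age test was significant in 3-7%, as expected when age has no role. Other runs of this kind gave higher lower bounds (22% at 53 events, 12% at 12), so the levels depend on the assumptions.

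**5. How precise would a product term be?** A rough check (438 patients aged 60-90, TSH 4.5-10, Poisson model) gave about 24-30% power with 53 events and 7-12% with 12, even if the TSH hazard ratio halves with each decade of age.

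**The case against.** The strongest reply is that the article mostly sets elderly limits against whole-population limits. It does so in the Abstract, the inclusion criteria and the follow-up section, and in the Discussion sentence just before the one on necessity. In that sense one higher cut-off for all elderly patients is itself the age-specific limit, and supporting it is what the study wants. This stands. A reader might infer that a result favouring one elderly cut-off would refute the study's hypothesis, but the documents do not support that. What remains is that, in this sense, the rival is one higher limit for adults of all ages. A cohort without younger adults cannot exclude it, and a product term fitted within the over-60s cannot either.

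A second reply is that the article lists no model terms, and the full plan may hold them. That is fair, so the missing term is not itself the error. The error is that a stated purpose is tied to a comparison that cannot deliver it. A fuller plan could add a term, but not a younger group.

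A third reply is that the rationale is overdiagnosis: healthy elderly people have higher TSH, and many labelled patients stay stable or recover. That is a legitimate argument for a reference interval. The 120 healthy people can describe the distribution, but this is not outcome evidence, and the Discussion ties necessity to the natural outcomes of patients.

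Finally, the simulated percentages rest on inputs that are not in the documents. That also stands: they illustrate the logic and do not estimate this study's error rate.

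**Conclusion.** The point holds in this form. The planned comparison can show whether higher TSH separates risk among people aged 60 or over, which is useful. It cannot show that limits should vary between age groups within the elderly, nor that the elderly limit must differ from that of younger adults. This follows from the design as described and needs no simulation.

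The size is best read from how close the cases are: 81% against 82% significant with and without a role for age, and at most 3 percentage points between decade-specific and single limits. The absolute rates, from 4% to 95%, carry no weight of their own.

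Two features of the article weaken the inference further. Criterion 3, read literally, admits only patients between the two limits, so the higher-TSH group might not be enrolled at all. And because the endpoint event changes its definition above age 80, differences in event rates between age bands would be partly built in.

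The change should be made: it is cheap and alters what the study may conclude. The data themselves remain useful.

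**What to change.** 1. **Data analysis.** Add, as a supporting analysis, a model with continuous log TSH, continuous age and their product. Use only outcomes defined identically at all ages, for example FT4 below the lower limit, or the MoCA-B and HAMD scores. Do not use the endpoint event that changes above age 80. Report estimated risk (or mean score) at fixed TSH values by age with confidence intervals, so that a reader can see whether the relation to TSH changes with age. Do not read a non-significant product term as proof that age has no effect. Since the start of treatment also depends on age in the follow-up section, say how follow-up after treatment starts is handled.

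2. **Discussion.** Limit the conclusion from outcomes to whether a higher limit separates risk among people aged 60 or over. Claim that limits must vary by age within the elderly only if the estimates in (1) support it. Do not claim from outcome data that the elderly limit must differ from that of younger adults.

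3. **Inclusion criteria.** Reconcile criterion 3 with the comparison of patients diagnosed under the two intervals (Discussion part of the Abstract; Study follow-up assessments).

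**Cost.** Items 1 and 2 need a few lines of analysis and rewording, on data already being collected. The price is a more modest conclusion, because the product term will be imprecise with 438 patients. Item 3 is a clarification of text, unless enrolment has followed the literal reading. In that case the between-group comparison itself has to be reconsidered.
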